#### Other outcome measures

Other outcome measures will include the following:Sex effectsMeasuring depth of anesthesia (BIS)Hemodynamic parameters (NIBP/Heart Rate (HR))Requirement of catecholaminesRespiratory parameters (Airway pressures and end-tidal carbon dioxide: CO_2_)Modified Aldrete scoreVAS pain in the PACUNausea in the PACUFrequency of vomiting in the PACUTime to readiness to be discharged from PACUPharmacoeconomicsPostoperative Quality Recovery Scale (PQRS) including the recovery on 1^st^ POD

### Participant timeline

A participant chart is shown in Additional file 1. Eligible patients, scheduled for surgery, will be presented to the anesthesia department for the general anesthesia consent preoperatively. Additionally, a blinded sub-investigator will explain the nature and purpose of the study to these patients and seek a written informed consent for the study (time point A, before surgery). The same investigator will collect the following baseline characteristics after the patient enrollment (time point A):AgeSexWeightHeightBMISmoking status (nonsmoker, current smoker-amount of pack years, ex-smoker)Contraceptives (woman - yes/no)Pre-existing diseases and medical/surgical historyClassification according to the American Society of Anesthesiologists (ASA)Apfel ScoreBaseline (Postoperative Quality Recovery Scale) PQRS testing prior to surgery (see Additional file 2)

Shortly before surgery on the same day (time point B), an unblinded investigator will randomize the patients with sequentially numbered, opaque, sealed envelopes (SNOSE).

The same unblinded investigator will perform anesthesia (time point C, surgery) and assess the intraoperative variables in the respective patient:Depth of anesthesia (BIS)Standard safety parameters: ECG, SpO_2_ and end-tidal CO_2_, and NIBPVentilation pressure parameters: Ppeak, Pmean, and PEEPType of performed surgeryRecording of the end-expiratory applied volatile anesthetic concentration/applied amount of propofol for maintenancePharmacoeconomics: Total amount of intraoperative required catecholamines, of additionally applied propofol as rescue medication, of wasted propofol at the end of the surgery in the propofol group and of intraoperative remifentanil and piritramide consumption.Time points of anesthesia induction, LMA insertion, administration of the study treatments, anesthesia and surgery durationFrequency of intraoperative (induction/maintenance) coughs and laryngospasms

The blinded investigator will enter the operating room at the time point T_0_, which starts with cessation of anesthesia and application of maximum fresh gas flow and predefines the measurement start-time point for the time variables. The unblinded investigator will ensure that the blinded individual is precluded from recognizing which anesthetic was used, by masking the ventilator. The blinded investigator will assess the following postoperative variables during time point D:

Assessment of airway reactionsFrequency of CE and LSEEmergence times: TSB, TLR, TOE, TRC, TSNThe modified Aldrete scores with a 10-point scale will be recorded 5 minutes after removal of LMA (see Additional file 3)

Time point E starts with admission of the patient to the PACU. The blinded investigator will assess the following variables:The modified Aldrete scores with a 10-point scale will be recorded every 15 minutes until discharge from the PACU (see Additional file 3)Time-point of readiness to be discharged from the PACU (Aldrete Score ≥9) (see Additional file 3)Assessment PQRS-T40, which is 40 minutes after the time point T_0_ (see Additional file 2).The VAS pain score will be self-evaluated and recorded by 100-mm visual analog scale (VAS) (with 0 corresponding to no pain and 100 corresponding to maximal pain) every 15 minutes after admission to the PACU. For postoperative analgesia, the patients will receive 0.05 mg kg^−1^ piritramide, in order to maintain a VAS pain score ≤30 mm

Other measurements in the PACU (blinded assessor) include the following:Nausea in the PACU will be evaluated using an 11-point verbal rating scale (VRS) (with 0 corresponding to no nausea and 10 corresponding to extreme nausea) at admission and discharge from the PACU and every 15 minutes in the PACUCount of vomiting in the PACUConsumption of piritramide in the PACU

Time point E: First post-op day: (telephone interview/ visit at ward):PQRS-D1 (see Additional file 2)

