### Other secondary objectives

Other secondary objectives are to determine the influence of gender on the patients’ reactions, the anesthesia safety variables including hemodynamic stability, the frequency and quantity of postoperative nausea, vomiting and pain, the discharge times, the pharmacoeconomics and the recovery on the first postoperative day (1^st^ POD).

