### Eligibility criteria

Investigators in each center will be selected and supervised by the local coordinating principal investigator. To ensure the blinding process, at least two investigators will be needed, when a patient is enrolled in this study. Therefore the screening and enrollment process will be performed according to the logistical possibilities of each center. All potential patients meeting the inclusion criteria will be documented in a screening log kept at each site. The reasons for not enrolling eligible patients will have to be stated in the screening log.

Inclusion criteria: A written informed consent prior to study participation will be mandatory. Participants in the study have to be adult patients between 18 and 75 years of age. They have to be scheduled to undergo elective surgery with a planned duration of 0.5 to 2 hours and the use of LMA. Both sexes will be included, and further inclusion criteria are an American Society of Anesthesiologists (ASA) physical status 1 to 3 and body mass index (BMI) <35 kg m^−2^.

Exclusion criteria: Subjects fulfilling one or more of the following exclusion criteria will not be included in the study: patients with planned additional regional and local anesthesia, with asthma or chronic obstructive pulmonary disease (COPD) grade IV, contraindication for the use of a LMA, known allergy or hypersensitivity to any drugs administered during this study. Furthermore, women who are pregnant, breast-feeding or of childbearing potential and not using adequate contraceptive methods will be excluded. Patients legally unable to give written informed consent, nonfluency in German language, with severe psychiatric or neuropsychiatric disorders or recent (<6 months) history of alcohol or drug abuse will not be included. The participation in a drug or device trial within the previous 30 days will be a further exclusion criterion.

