### General interventions for all patients

Premedication: All patients will receive an oral administration of up to 7.5 mg midazolam 30 to 45 minutes preoperatively, according to the clinical routine of each center.

Induction: Upon arrival into the surgery room, a standard monitoring will be applied to all patients. This will consist of continuous electrocardiogram (ECG), measurement of non-invasive blood pressure (NIBP) and peripheral oxygen saturation (SpO_2_). A connection of Bispectral Index (BIS) monitoring will follow. After pre-oxygenation with oxygen (FiO_2_ = 1.0) for 3 minutes via face-mask, all patients will receive remifentanil injection via infusion pump at an initial rate of 0.5 μg kg^−1^ over 60 seconds and 1.5 to 2.5 mg kg^−1^ (plus 2 ml lidocaine 1 %) propofol by bolus titration intravenous (i.v.). After loss of consciousness, the LMA will be inserted and blocked with a cuff pressure at 30 cm H_2_O. Teeth marks on the device will help to check the correct insertion. The leakage will have to be controlled by applying a positive airway pressure of 25 cm H_2_O. A reassessment will take place after 5 minutes. If the LMA is not tight, a replacement of LMA will follow. After a second failure of LMA placement, an alternative airway will be applied.

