Maintenance: All patients will receive a postoperative nausea and vomiting (PONV) prophylaxis with 8 mg dexamethasone and 4 mg ondansetron, if the Apfel-Score is ≥2. Analgesia will be maintained with remifentanil injection via infusion pump at a rate of 0.15 μg kg^−1^ min^−1^. Dosage will be adapted according to clinical needs based on the patient’s hemodynamic (difference of NIBP and HR greater than 20 % from baseline), autonomic (sweating, salivation, or flushing) and somatic (movement or swallowing) signs. Twenty minutes before the estimated end of surgery, all patients will receive 0.05 to 0.1 mg kg^−1^ piritramide and 15 mg kg^−1^ metamizole i.v. The inspired oxygen concentration will be adjusted to 35 to 50 %, or above this range if medically indicated. The end-expiratory CO_2_ level during the maintenance of anesthesia should be kept between 36 and 45 mmHg. The use of muscle relaxants is undesired, except for emergency situations. Spontaneous breathing or controlled ventilation with LMA will be applied during maintenance of anesthesia, according to the standard operating procedure of each participating center. Inspired desflurane concentrations of >8 vol. % and sevoflurane >2.2 vol. % have to be avoided. The systolic blood pressure should be kept at ≥90 mmHg (or ≥65 mmHg for mean arterial blood pressure), and a relative variation > 20 % from baseline values has to be avoided and requires appropriate treatment. If indicated additional bolus injection of propofol is permissible in patients.

End of anesthesia: At five minutes before planned termination of surgery, remifentanil will be discontinued. The LMA will be removed when the upper airway reflexes are fully recovered and the respiratory function is adequate (regular spontaneous breathing with a frequency of at least eight breaths per minute and SaO_2_ >95 %) and when the patient opens his/her eyes on request or is able to follow any other requests. In addition, the patient has to be hemodynamically stable before removal of LMA. The patients will be admitted to the Post Anesthesia Care Unit (PACU) following surgery. They will receive 0.05 mg kg^−1^ piritramide if the visual analog scale (VAS) for pain is more than 30.

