### Specific interventions

There will be three parallel intervention groups receiving different anesthetics for the maintenance of anesthesia after the induction phase and placement of the LMA.

Group 1 will receive desflurane. After setting the fresh gas flow at 2l min^−1^, the desflurane vapor will be turned to 12 vol. % until the desired end-expiratory target concentration of 0.8 MAC (minimal alveolar concentration) or 4 to 5 vol. % desflurane is achieved. Thereafter, a reduction of the fresh gas flow to 500 to 1,000 ml will be performed to maintain anesthesia. Desflurane concentration will be adjusted to maintain a BIS index value between 40 and 60. Five minutes before estimated termination of surgery, the vapor will be set to zero. At the end of the surgery maximum fresh gas flow will be applied. This time-point will be defined as time zero (T_0_).

Group 2 will receive sevoflurane. After setting the fresh gas flow at 2l min^−1^, the sevoflurane vapor will be turned to 8 vol. % until the desired end-expiratory target concentration of 0.8 MAC or 1.2 to 1.4 vol. % sevoflurane is achieved. Thereafter, a reduction of the fresh gas flow to 500-1000ml will be performed to maintain anesthesia. Sevoflurane concentration will be adjusted to maintain a BIS index value between 40 and 60. Five minutes before estimated termination of surgery, the vapor will be set to zero. At the end of the surgery maximum fresh gas flow will be applied. This time-point will be defined as time zero (T_0_).

Group 3 will receive propofol via infusion pump at an initial rate of 5 to 7 mg kg^−1^ h^−1^ propofol and then adjusted to maintain a BIS index value between 40 and 60. Five minutes before estimated termination of surgery the propofol concentration will be halved. Propofol will subsequently be discontinued and maximum fresh gas flow with F_i_O_2_ = 1.0 will be applied at the end of surgery. This time-point will be defined as time zero (T_0_).

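### Discarded propofol is recorded in the propofol group only, so rescue-bolus remainders, and possibly induction remainders, go uncounted in the two volatile arms

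*Protocol article*

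**What the plan says.** The Participant timeline section lists the pharmacoeconomic data that the unblinded investigator collects during surgery. Two items concern propofol. One is the amount "of additionally applied propofol as rescue medication", which carries no limit by arm and counts what was given. The other is the amount "of wasted propofol at the end of the surgery in the propofol group", which is limited to one arm. The remaining items on the list (catecholamines, remifentanil, piritramide) carry no arm limit. Separately, the section records the amount of propofol applied for maintenance.

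Propofol is not confined to one arm. Under General interventions for all patients, everyone receives 1.5 to 2.5 mg/kg as a titrated bolus at induction. The maintenance paragraph of the same section adds: "If indicated additional bolus injection of propofol is permissible in patients". Only the maintenance infusion is specific to an arm: "Group 3 will receive propofol via infusion pump at an initial rate of 5 to 7 mg"/kg/h, then adjusted to the BIS target (Specific interventions).

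Other secondary objectives names "the pharmacoeconomics and the recovery on the first postoperative day", Other outcome measures lists pharmacoeconomics, and Statistical methods presents economic results on all randomized patients.

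**The concern.** A cost comparison between arms needs each cost component measured by the same rule in every arm. Here propofol is opened in all three arms, but the discarded part is collected in one. In the volatile arms an opened container can be charged only for what was injected. In the propofol arm it can be charged for what was injected plus what was thrown away. An analysis plan written later can choose how to price these quantities, but it cannot recover waste that was not recorded.

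At stake is one listed outcome and its direction. Under Risk benefit assessment the article expects faster emergence with desflurane to improve cost effectiveness, and any waste left out of the volatile arms would work toward that conclusion. This is separate from how volatile consumption is measured. The gap would remain if that were measured perfectly.

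**Working it through.** The article states no cost or waste figure, so there is nothing to reproduce. The check has two parts: which remainders the rule treats unequally, and how large the induction part could be.

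**Which remainders are treated unequally**

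- *Infusion remainder.* It arises only in the propofol group and is recorded there. It has no propofol counterpart in the volatile arms, so there is no bias.
- *Rescue-bolus remainder.* The amount given is recorded in all arms. What is left over falls under the literal words of the waste item in the propofol group and under no item in the volatile groups. Boluses are given after the arms diverge, so equal use cannot be assumed.
- *Induction remainder.* The outcome depends on what the item means:
  - If it covers all propofol left at the end of surgery, induction remainders are counted in the propofol group and not in the volatile groups.
  - If the propofol group carries the induction remainder into the infusion, it is used there, but discarded uncounted in the volatile groups.
  - If it covers the infusion remainder alone and induction remainders are discarded separately everywhere, they are uncounted in all arms. They are then equal in expectation under randomization, and cancel.

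The uncounted amount is zero or more, and it lies in the volatile arms. If waste is priced, leaving it out can lower only those arms' cost.

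**Possible size of the induction part**

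Inputs from the article: induction dose 1.5 to 2.5 mg/kg; initial maintenance rate 5 to 7 mg/kg/h; "elective surgery with a planned duration of 0.5 to 2 hours"; 117 patients per arm. Assumptions not in the article: body weight 80 kg; a 200 mg container opened for each patient; infusion at the initial rate for the planned duration.

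- Induction use = dose × weight: 1.5 × 80 = 120 mg to 2.5 × 80 = 200 mg.
- Remainder = containers opened × 200 mg − use: 200 − 120 = 80 mg, down to 200 − 200 = 0 mg.
- Two volatile arms: 2 × 117 = 234 patients. The ceiling, if all were at the lowest dose, is 234 × 80 mg = 18,720 mg, about 18.7 g. The floor is 0.
- Maintenance use in the propofol arm: 5 × 80 × 0.5 = 200 mg to 7 × 80 × 2 = 1,120 mg.
- The 80 mg remainder occurs only at the lowest induction dose, so it must be compared with propofol-arm use at that same dose: 120 + 200 = 320 mg to 120 + 1,120 = 1,240 mg. This gives 80/320 = 25 % and 80/1,240 = 6.5 %. At the highest induction dose the remainder is 0 mg, so the full range is 0 to 25 %.

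Sensitivity to weight, same container, at 1.5, 2.0 and 2.5 mg/kg:

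| Weight | Induction remainder (mg) |
|---|---|
| 60 kg | 110, 80, 50 |
| 70 kg | 95, 60, 25 |
| 80 kg | 80, 40, 0 |
| 90 kg | 65, 20, 175 |

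The 175 mg arises because 225 mg needs a second container. Over 60 to 90 kg the computed range is therefore 0 to 175 mg.

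For scale, take maintenance containers of 500 or 1,000 mg (also assumed) and infusion for 0.5, 1 or 2 h. The infusion remainder at 80 kg then runs from 500 − 5 × 80 × 1 = 100 mg to 2,000 − 1,120 = 880 mg. This waste is properly attributed to the propofol arm, and under these assumptions it is usually larger than the part in dispute.

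**The case against.** The strongest reply is that the item simply means what is left of the infusion. It refers to the end of surgery and to the one arm with a propofol infusion, and induction propofol is not a listed cost item in any arm. On that reading, recording waste in one arm is correct attribution, and induction remainders cancel. This is a natural reading and may be the intended one. It would remove most of the concern, but it is not written down, and the literal words cover anything left over. It also leaves rescue-bolus remainders unrecorded in the volatile arms.

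A reader might go further and infer that the whole cost comparison is tilted against propofol by construction. The article does not support that. Infusion waste is a genuine cost of that strategy. Nothing says that one container serves both induction and infusion, or that propofol is drawn up in advance for boluses in every patient; a bolus is only permitted when indicated. The pricing rule is not shown and may properly sit in the full protocol or the analysis plan. Its absence is no fault here, but without it no effect on cost can be demonstrated.

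It is also fair to say that, by the dates under Trial status (start at the end of February 2015, predicted end September 2015), a new field would cover only some patients.

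**Conclusion.** The point holds in a narrow form. The article fixes a collection rule that differs by arm for a drug used in all arms. Rescue-bolus remainders, and induction remainders under two of the three readings, are uncounted in the volatile arms only. If waste is priced, the direction is toward a lower cost for desflurane and sevoflurane relative to propofol.

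The size is unknown and may be zero. The 0 to 80 mg per volatile-arm patient rests on an assumed 80 kg and a 200 mg container, covers induction only, and cannot be turned into money without prices. No figure can be given for bolus remainders, because the article gives no bolus frequency.

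The consequence is minor. It touches one component of one outcome among the other outcome measures. Desflurane versus sevoflurane is not affected, since both are recorded alike. Neither is the time to state the date of birth or the noninferiority test on cough.

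**What to change.** Remove the arm limit: record the amount of propofol discarded in all three groups, state that the item includes induction and rescue-bolus remainders, and cost propofol in every arm on the same basis, given plus discarded. Infusion waste then stays with the propofol arm, where it belongs, and the other remainders are treated alike everywhere.

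The cost is small: an existing eCRF item is opened for two more groups, with no change to treatment, the primary endpoint or the sample size. The downside is that, for patients already treated, the value has to be taken from the anesthesia record or reported as missing. The report should say how many patients in each arm this concerns.

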### Sample size

Sample-size estimates for both considerations (superiority and noninferiority) were calculated separately. All sample sizes were calculated using a type 1 error, α = 0.05, and power of 0.80. The primary outcome calculations were carried out based on a one-way analysis of variance (same n) with three groups. The variances and means were estimated for the primary outcome variable time to state the date of birth from our meta-analysis [4]. For the sevoflurane, propofol and desflurane groups, means were set to 8.75, 6.8 and 5.6 minutes, respectively. A standard deviation of 3 minutes was considered (these parameters correspond to an effect size (f) of 0.43). A sample size of 19 patients per group is needed to detect such an effect for our superiority hypothesis.

The sample size for the noninferiority hypothesis was calculated based on the secondary outcome variable cough overall (CO). Using the normal approximation to the binomial and assuming a proportion of the outcome in the population between 0.07 and 0.10 and noninferiority bound of 0.20 a sample size of 81 and 112, respectively, is required to claim noninferiority. The margin delta of 20 % was chosen for clinical considerations. We claim that a difference of cough occurrence up to 20 % is clinically not relevant. This is justified by the result of our meta-analysis [4], where the identified coughs had never lead to a serious impact on the patients’ outcomes.

The sample size calculation for noninferiority of treatment is based on a sample size formula published by Blackwelder [7]. Considering data from the literature, a dropout rate of 5 patients per group (for example, requirement of endotracheal intubation, protocol deviations and losses for first postoperative day- follow up) is expected. We decided therefore to include 117 patients per group, to cover the calculated sample size of 19 + 5 patients per group for the superiority hypothesis as well as 112 + 5 patients for the noninferiority hypothesis. Altogether, there will be 351 randomized patients.

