Access to randomization is reserved solely to the intraoperative investigator and has to be done shortly before surgery. The time point of envelope opening, the patient initials and the screening number of the patient will be written on the appropriate envelope before it is opened. The envelopes have to be safely stored in the intraoperative patient file. Within a center, the randomization number will occur in succession. The number will contain information about the randomizing study site and the patient sequence. The randomization number will consist of six digits, the first three for the center and the last three for the patient, for example, 001 to 001 (for center 001 and the first patient included). This randomization code will be used to label all information collected for each patient. The monitors of the study will check carefully that the envelopes were really used in the correct sequence and that the signed informed consent occurred definitively before opening of the randomization envelope.

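### No analysis statement names center, although envelopes run within each center and premedication and ventilation follow center routine; adding it is a cheap, small gain in precision

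*Protocol article*

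**What the plan says.** **Sizing.** The Sample size section of the protocol article sizes the primary outcome "based on a one-way analysis of variance (same n) with three groups". For sevoflurane, propofol and desflurane, "means were set to 8.75, 6.8 and 5.6 minutes, respectively". It adds: "A standard deviation of 3 minutes was considered (these parameters correspond to an effect size (f) of 0.43". This gives 19 patients per group for superiority. The noninferiority calculation for cough raises the number to 112 per group, and the allowance for dropout to 117.

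**Analysis.** The Statistical methods section assigns parametric data to ANOVA and count data to Fisher's exact or the Chi-square test. Noninferiority is judged on an upper confidence bound. The section lists no model factors, says that no further analyses are foreseen, and announces a full statistical analysis plan (SAP) before unmasking.

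**Allocation.** Under Randomization, the biostatistician sets the number and length of blocks and gives envelopes to the principal investigator of each center. "Within a center, the randomization number will occur in succession", and the first three of the six digits identify the center.

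**Center differences.** Under General interventions for all patients, oral midazolam of up to 7.5 mg is given "according to the clinical routine of each center". Spontaneous breathing or controlled ventilation "will be applied during maintenance of anesthesia, according to the standard operating procedure of each participating center".

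**The concern.** Center looks like the unit within which patients are allocated, and the protocol lets centers differ in two respects that could affect the outcomes. A sedative premedication may plausibly lengthen emergence, and ventilation mode may plausibly affect cough. When allocation is balanced within a group that predicts outcome, the treatment contrasts are already free of differences between groups. An analysis that omits the group still leaves that variation in its error term. Standard errors are then larger than they need to be.

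What is at stake is precision. It matters most for desflurane versus propofol, where the planned difference is 6.8 − 5.6 = 1.2 minutes, against 8.75 − 5.6 = 3.15 minutes for sevoflurane.

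**Working it through.** **Inputs from the Sample size section.** Means 8.75, 6.8 and 5.6 minutes; SD 3; α = 0.05; power 0.80; 112 evaluable patients per group. Four centers (Study setting). The share R of TSB variance lying between centers is not given; 0, 1, 5, 10 and 20% are assumed.

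**1. The plan's own figure.** The grand mean is 21.15/3 = 7.05. Squared deviations are 2.89, 0.0625 and 2.1025, with sum 5.055. So f = √(5.055/3)/3 = 1.298/3 = 0.433, matching 0.43. With 19 per group, N = 57 and the noncentrality is N·f² = 57 × 0.1872 = 10.67 on 2 and 54 degrees of freedom. Power is 0.819, so 19 reproduces.

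**2. Omnibus test with center added.** The residual SD becomes 3√(1−R) and the error degrees of freedom fall from N−3 to N−6. The number per group for 80% power is 19 at R = 0 or 1%, 18 at 5%, 17 at 10% and 15 at 20%. At 112 per group, power exceeds 0.9999 with or without center.

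**3. Desflurane versus propofol, two-sided 0.05, 112 per group.** SE = 3√(1−R)·√(2/112); noncentrality = 1.2/SE. With center in the model:

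| R | SE (min) | Noncentrality | 95% CI half-width (min) | Power |
|---|---|---|---|---|
| 0 | 0.401 | 2.99 | 0.79 | 0.85 |
| 1% | 0.399 | 3.01 | 0.78 | 0.85 |
| 5% | 0.391 | 3.07 | 0.77 | 0.86 |
| 10% | 0.380 | 3.16 | 0.75 | 0.88 |
| 20% | 0.359 | 3.35 | 0.70 | 0.92 |

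The usual calculation without center (SD 3) gives 0.85 whatever R is.

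That comparison somewhat flatters the adjustment. Under balance within center, the estimated difference already varies with the smaller SD, and only its reported SE is too large. The power of the unadjusted test is then about Φ[(2.993 − 1.967)/√(1−R)], which is 0.85 / 0.86 / 0.87 at R = 5 / 10 / 20%. The net gain in power is therefore nearer 1 / 2 / 4 points. The gain in reported interval width is as tabulated.

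**4. Type I error without center.** In a simulation with 20,000 runs per R, four unequal centers (39, 33, 26 and 19 patients per arm, 117 in all) and allocation balanced within center, the omnibus test rejected a true null with frequency 0.049 / 0.043 / 0.036 / 0.024 at R = 0 / 5 / 10 / 20%. With center in the model the range was 0.048 to 0.052. An approximation agrees: exp[−3.02/(1−R)] gives 0.049 / 0.042 / 0.035 / 0.023.

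**5. Cough, illustration only.** At 10% cough and 112 per group, the SE of the risk difference is √(2 × 0.10 × 0.90/112) = 0.040. Suppose half the patients were in centers with 5% cough and half in centers with 15% (assumption). Center would then explain 0.05²/0.09 = 2.8% of the variance, and stratifying would cut the SE by 1 − √(1 − 0.028) = 1.4%.

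**The case against.** The strongest reply is that the protocol does not commit to an analysis without center. The one-way ANOVA is described where the trial is sized. The Statistical methods section says ANOVA without calling it one-way, and a model with treatment and center fits that wording. The SAP is announced, is not shown here, and may already include center; model factors are often settled there. A reader might infer that the primary analysis is fixed as a one-way ANOVA ignoring center, but the documents do not establish this.

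Nor do they say that randomization is stratified by center. Center-wise lists are a reasonable reading of the envelope logistics, and no more than that.

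A reader might also infer that omitting center makes the test invalid or biased, or leaves the trial short of power. Neither follows. The error is on the conservative side, the omnibus test has power to spare, and the desflurane–propofol contrast is already above 0.80 without adjustment. A material loss on the noninferiority bound is likewise not shown; the illustration above suggests very little.

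All of this stands, and it limits the point to a recommendation. What survives is that every method the article does name is unadjusted as described, that it foresees no further analyses, and that center is visibly part of both allocation and care.

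**Conclusion.** The point holds as a low-severity improvement to the stated method. It corrects no figure: f = 0.43 and 19 per group both reproduce. The benefit depends on two things the article does not settle: that allocation is balanced within center, and that centers differ in TSB. If both hold and center explains 5 to 20% of the variance, naming it restores the type I error to about 0.05 and narrows the desflurane–propofol interval by roughly 2.5 to 11%. It brings that contrast's power to 0.86–0.92, against 0.85 nominally. If center explains about 1% or less, there is practically no gain and practically no cost.

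**What to change.** In Statistical methods, and in the SAP before unmasking, state the primary model as ANOVA of TSB on treatment plus center (four levels), with the desflurane contrasts taken from that model. Base the upper confidence bound for cough on a center-stratified risk difference, for example with Mantel–Haenszel weights. State in Randomization whether the lists are stratified by center.

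The cost is a few sentences and three error degrees of freedom: 345 instead of 348 with 351 patients. No sample-size change follows. Nothing in this argument calls for a log scale or for age and sex as covariates, so neither is requested.
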